### Data and biosample collection

The pre-pregnancy BMI is calculated using the measured weight at study entry minus the mother’s self-reported GWG. Body weight is measured by trained research assistants using a body impedance Tanita Body Composition Analyzer BF-350 scale (Tanita, IL, USA) at 12–17 weeks of gestation, 26–28 weeks of gestation, 36–38 weeks of gestation, three months postpartum (self-reported weight only), and six months postpartum. GWG is calculated by subtracting the weight at the 36–38 weeks of gestation study visit by the pre-pregnancy weight. Adjustments such as rate of GWG will be made to account for gestational age at delivery, including pre-term births.

Fasted maternal blood samples for metabolic and bone health biomarkers are collected at 12–17 weeks of gestation, 36–38 weeks of gestation, and at six months postpartum; venous cord blood is collected at delivery. Serum is collected in serum-separating with gel (SST™) vacutainers and in spray-coated silica vacutainers; plasma is collected in sodium fluoride/ Na_2_ ethylenediaminetetraacetic acid (Na2EDTA) vacutainers. Sample are centrifuged for 10 min at 3000 rpm at 4 °C; serum separator tubes are spun for an additional 5 min, aliquoted, and stored at − 80 °C. Samples are batched to include all samples from each mother for analysis in our laboratories when participants have completed the study. Fasting plasma glucose is determined using a hexokinase photometric assay (Architect kit, Abbott, Abbott Park, IL, USA). Serum triglycerides are analyzed using a glycerol phosphate oxidase photometric assay (Architect kit, Abbott, Abbott Park, IL, USA) completed by Hamilton Health Sciences Regional Laboratory Medicine Program. Serum leptin and insulin are analyzed using Luminex® human premixed multi-analyte enzyme-linked immunosorbent assay (ELISA) kit supplied by R&D Systems (Minneapolis, MN, USA). Serum adiponectin and C-reactive protein are analyzed by Luminex® premixed multi-analyte ELISA kit supplied by R&D Systems. Bone formation is assessed by measuring serum PINP by ELISA (Cloud Clone Corp., Houston, TX, USA). Bone resorption is assessed by measuring serum CTX-I by (Serum Crosslaps (CTX-1) ELISA, product code AC-02F1 Immunodiagnostic Systems, UK). Growth is assessed by measuring serum IGF-1 by ELISA (R&D Systems, Minneapolis, MN, USA). All standards and samples are analyzed in duplicate, following the manufacturer’s instructions. A serum quality control is run in triplicate at the beginning and end of each ELISA plate to calculate inter- and intra-assay coefficients of variability. Serum vitamin D metabolites are measured by liquid chromatography tandem mass spectrometry (LC-MS/MS) using a Waters AQUITY Tandem Quadropole Detector coupled to an AQUITY UPLC system (Waters Corporation), after extraction that includes a saponification step as adapted from Hymoller [47]. Accuracy is determined using the certified Vitamin D analytes serum-based standard reference material (SRM 972a) from the US National Institute for Standards and Technology (NIST; National Bureau of Standards, Washington, DC, USA) [48]. Precision is measured using a serum quality control in all runs of samples tested, allowing calculation of inter- and intra-assay coefficients of variability.

DNA extracted from maternal and cord blood plasma samples will be purified using the Chemagen 500 MSM I (PerkinElmer chemagen Technologie GmbH, Baesweiler, Germany) and genotyped using the Human Core Exome Bead Chip by Illumina. The chip is specifically designed to allow imputation of up to 18 million markers in multi-ethnic populations. Data cleaning and quality control of SNPs data are done according to the guidelines published by Winkler et al. [49].

Bone mass is measured by DXA scan using the research dedicated QDR®4500 series Hologic Inc. Discovery™ DXA machine (Waltham, MA, USA; Adult whole body software version 12.3.1 and Infant whole body software) at the McMaster University study site and the General Electric-Luna iDXA (Ames Medical enCORE, Version 14.1, Waukesha, WI, USA; CoreScan, GE) at the Western University study site. Daily quality control tests are conducted using an artificial L_1–4_ lumbar spine made from hydroxyapatite encased in epoxyresin. Weekly, a calibration test is performed using a step phantom (composed of soft-tissue and lean-tissue equivalent materials); at this time, the uniformity test is also performed to evaluate the contribution of air molecules to the attenuation of the X-rays. The coefficient of variations for BMC and BMD were 0.65% and 0.38%, respectively (Hologic Inc., Bedford, MA, USA) in our past study [37]. Inter-site comparison of DXA measures is conducted by having two phantoms (i.e. Hologic lumbar spine phantom (#2603), BFP® phantom) tested at both study sites. This provides a cross-calibration standard and enables us to account for inter-site differences and to harmonize results. It also allows for verification of the instrument stability over the course of the study.

At six months postpartum, bone scans are performed on mothers and infants at six months by staff following a standard operating procedure. Mothers are dressed in regular clothes without any metal parts or in a light hospital gown, while infants are in a clean diaper only. The primary outcome assessor, who has expertise in analyzing DXA scans, reviews all scans from both study sites. This ensures consistency in analysis across all participants at both study sites. If objects are included in the scan such as a child’s toy, a sub-regional analysis is done to isolate and subtract the object’s contribution to overall results. If considerable movement artifacts are seen in infant scans, the well-captured limb is used as a surrogate for the one with movement [50]. Any scans with unsalvageable distortions due to movement are not included. Z-scores are calculated for all BMC and BMD results using data from an age- and sex-specific standard curve. Results for women are interpreted as z-scores in reference to an adult women population embedded in the Hologic software. Results for infants are expressed as whole body minus the head BMC and BMD. Data are interpreted as z-scores in reference to an infant population from in-house data collection on normal healthy term infants from birth to one year of age.

All participants receive instructions to complete a standard three-day food intake record at 12–17 weeks of gestation, 26–28 weeks of gestation, 36–38 weeks of gestation, and six months postpartum. The food record includes two weekdays and one weekend day, as used previously in pregnant women [39]. It captures food and beverage intake as well as drug and supplement (vitamin and mineral) intake. Trained assessors analyze all food records using standard operating procedure on the computer-based Nutritionist Pro Software (Axxya Systems, Stafford, TX, USA). Nutritionist Pro computes the average amount of nutrients consumed per day.

Physical activity level is assessed through wearing a BodyMedia Sensewear Pro II armband monitor device (BodyMedia, Pittsburgh, PA, USA) in all participants for the same three days (as food monitoring above) in their work/home environment. These small devices are comfortable and easily wearable on the arm [38]. The data collected for three days at each visit (12–17, 26–28, and 36–38 weeks of gestation and six months postpartum) includes daily steps, daily energy expenditure, and minutes of activity level in Metabolic Equivalent of Task (MET; very vigorous, vigorous, moderate, sedentary). The Sensewear unit does not provide feedback to the participant.

Pregnancy and infant outcomes are obtained from participant’s medical records. Details are extracted about Cesarean section and/or vaginal delivery. For infant outcomes, data regarding gestational age, birth weight, birth length, birth head circumference, 1-min and 5-min Apgar scores, complications related to birth, and feeding practices at birth are extracted.

Infant weight and length at birth are recorded from medical charts and at three months of age as reported by the mother during the telephone interview. At the six-month visit, trained assessors measure infant weight by electronic scale (Medela BabyWeigh, McHenry, IL, USA), length using a measuring board for term infants (Pediatric Stadiometer, Ellard Instrumentation Ltd., Monroe, WA, USA), and head circumference using a constant-tension measuring tape (OHAUS, Dundas, ON, Canada), following standard operating procedures.

Infant feeding practices over the first three months are recorded by phone call and at six months in person using a standardized questionnaire administered by a trained assessor [51]. The questionnaire includes feeding history, duration and extent of breastfeeding, introduction of solid foods, and use of vitamins and supplements.

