## Outcome measurements

Primary and secondary outcomes are summarized in Table 2 and described below.Primary outcome○ GWGSecondary outcomes○ Maternal and cord blood circulating bone markers: PINP, CTX-I, IGF-1, 25(OH)D, 1,25dihydroxyvitamin D○ Maternal bone status at six months postpartum: whole-body bone mineral content (BMC), whole body BMD, lumbar spine BMD○ Infant bone status at six months of age: whole body minus the head BMCOther outcomes○ Maternal body weight and fat mass○ Maternal metabolic status (including fasting glucose and lipid profiles, leptin and adiponectin)○ Maternal blood pressure○ Maternal pregnancy outcomes such as gestational diabetes and pre-eclampsia○ Infant birth outcomes such as birth weight and body fat mass at six months○ Safety outcomes○ Quality of life using the EQ-5D questionnaire○ Healthcare costs○ Maternal and cord blood gene variant profiles

**Table 2 Tab2:** Analysis plan: objectives, outcomes, hypotheses, and methods of analysis

Objective	Hypothesis	Outcome measure (type of outcome: B = binary or C = continuous)	Methods of analysis
1. Primary	An experimental combined Nutrition + Exercise intervention will increase the percentage of pregnant women who achieve GWG within current recommendations when compared with standard care provided in the primary care community setting	Proportion of women who are within the BMI appropriate GWG according to the IOM guideline for GWGs (B)	Logistic regression
2. Secondary	An experimental combined Nutrition + Exercise intervention will lead to better maternal and child bone health outcomes when compared to standard care	*• Maternal and cord blood circulating bone markers (C)* ○ Bone biomarkers: PINP, CTX-I, IGF-1, 25(OH)D, 1,25(OH)_2_D *• Maternal bone status at 6 months postpartum (C)* ○ Whole body bone mineral content, whole body BMD, lumbar spine bone mineral density by DXA scan *• Maternal fat mass (C)* *• Maternal blood glucose, lipid profile, leptin, and adiponectin* *• Maternal blood pressure (C)* ○ Diastolic BP ○ Systolic BP *• Maternal pregnancy outcomes (B)* ○ Gestational diabetes ○ Pre-eclampsia *• Infant bone status at 6 months of age (C)* ○ Whole body minus the head bone mineral content by DXA scan *• Infant outcomes* ○ Birth weight z-score(C) ○ Body fat mass (B)	Regression analysis *We will use logistic regression for binary outcomes and linear regression for continuous outcomes

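### Plasma is named as the DNA source for maternal and cord array genotyping, and no cell fraction is listed, so the gene-variant outcome is of doubtful reliability as written

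*Protocol article*

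**What the plan says.** The list under Outcome measurements ends its Other outcomes with "Maternal and cord blood gene variant profiles". Table 2 gives this item no hypothesis and no method of analysis.

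The section Data and biosample collection describes how the profiles are obtained. The specimen is stated outright: "DNA extracted from maternal and cord blood plasma samples will be purified using the Chemagen 500 MSM I". The DNA is then "genotyped using the Human Core Exome Bead Chip by Illumina", and the article adds: "The chip is specifically designed to allow imputation of up to 18 million markers in multi-ethnic populations".

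The same section describes the blood fractions. For serum: "Serum is collected in serum-separating with gel (SST™) vacutainers and in spray-coated silica vacutainers". For plasma: "plasma is collected in sodium fluoride/ Na_2_ ethylenediaminetetraacetic acid (Na2EDTA) vacutainers". Processing is given as "Sample are centrifuged for 10 min at 3000 rpm at 4 °C", followed by aliquoting and storage at −80 °C. Maternal blood is "collected at 12–17 weeks of gestation, 36–38 weeks of gestation, and at six months postpartum"; cord blood is taken once, at delivery. The article does not say which maternal draw supplies the DNA.

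**The concern.** Germline DNA sits in nucleated cells, and plasma is by definition the fraction left after those cells are removed. What remains is a small quantity of short, cell-free fragments, which is a poor input for a genome-wide array and for imputation built on its calls. This applies to mother and cord alike.

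For the mother there is a second difficulty. Cell-free DNA in plasma drawn during pregnancy comes partly from the fetus, so such a sample is not a clean maternal genotype.

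At stake is the usefulness of the gene-variant data. Timing also matters: cord blood is available only once, and a cell layer that is not set aside when the plasma is removed may not be there later.

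**Working it through.** The documents give no DNA yield, array input requirement, call rate or fetal fraction, so there is no figure of the plan to reproduce. The check is a comparison of statements.

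1. **Specimen named for DNA.** Plasma, for both mother and cord (DNA paragraph of Data and biosample collection). This is a positive statement, not a gap.
2. **Fractions listed as collected.** Serum from gel and silica tubes, and plasma from sodium fluoride/EDTA tubes (blood-handling paragraph, same section). No whole-blood, buffy-coat or pellet aliquot is named there or elsewhere in the article, so nothing in the text corrects item 1.
3. **Use of the DNA.** A SNP array with imputation, which needs intact germline DNA of adequate amount. Set against item 1, the stated specimen and the stated use do not fit. That plasma DNA is scarce and fragmented is general laboratory knowledge, not a figure from the article.
4. **Maternal draw.** Three draws are listed: two in pregnancy (12–17 and 36–38 weeks) and one at six months postpartum. Fetal admixture arises only if one of the two pregnancy draws is used. It does not apply in the same way to cord blood.
5. **Status of the work.** Purification is described in the future tense, samples are held in batches until participants finish, and Trial status reports active recruitment. At the time of writing, the specimen could still be corrected for later participants.
6. **Reach.** One entry under Other outcomes. Gestational weight gain, the bone outcomes and the Power calculation do not use genotype data.

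**The case against.** The strongest reply is that this is a wording slip. The authors may mean DNA from the cell layer of the tubes used for plasma. The tube list is introduced as blood for metabolic and bone markers and need not be a full inventory of what is stored. A journal article also condenses the protocol, and aliquot handling belongs in laboratory procedures. Much of this stands. The absence of a pellet step from the article does not prove that none exists. It does not remove the point, because the article names the specimen and the one it names is unsuitable. Under either reading, that sentence needs correcting or confirming.

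A reader might infer more than the text supports:

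- **That the cells are discarded and lost for good.** No passage says so. For mothers, the six-month draw gives a further opportunity.
- **That many samples would fail quality control.** No yield or call rate is given, and SNP cleaning and quality control to a published guideline are planned.
- **That a mother-versus-infant genotype comparison would be biased.** No such comparison is specified.
- **That fetal DNA would make the maternal calls wrong.** The documents give no fetal fraction. If a share f of the plasma DNA is assumed to be fetal, the foreign-allele share where the mother is homozygous and the fetus heterozygous is f/2. For f = 5%, 10% and 20% this is 2.5%, 5% and 10%, against clean genotype positions of 0, 50 and 100%. On an array, which measures signal intensity, a shift of that size blurs the clusters but does not by itself turn one call into another. The amount and length of the DNA are the larger worry.

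**Conclusion.** The point holds as a minor one. The article names an unsuitable specimen for array genotyping and lists no cell fraction that would supply a suitable one. Followed as written, the gene-variant profiles of up to 242 mothers and their cord samples would be of doubtful reliability. How many would be unusable cannot be sized from the documents.

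The conclusion assumes that plasma is meant literally. If it is a slip for the cell layer, the defect is confined to the text. The fetal-DNA part holds only if plasma from a pregnancy draw is genotyped.

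**What to change.** Three changes to Data and biosample collection:

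1. Name the cell fraction (buffy coat or pellet) of the maternal and cord sodium fluoride/EDTA tubes as the DNA source, after checking this against what is in storage.
2. State which maternal draw supplies the DNA. The six-month postpartum draw avoids fetal admixture.
3. Add to the blood-handling paragraph that the cell fraction is aliquoted and frozen when the plasma is removed.

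Where only pregnancy plasma exists for a woman, do not treat it as her germline sample.

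The cost is one extra aliquot per tube already drawn and spun, plus wording in the protocol and laboratory procedures; no extra blood is needed. Participants with no stored cell fraction drop out of the genotype set. If the six-month draw is chosen, so do mothers who do not attend that visit; the article gives no retention figure for it.

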### Study management and governance

This RCT is led by investigators from McMaster University (Department of Pediatrics, Department of Family Medicine, Department of Obstetrics and Gynecology, Department of Health Research Methods, Evidence and Impact, and School of Nursing) and Western University (School of Kinesiology) as well as practitioners from the City of Hamilton Public Health, all located in Ontario, Canada. The oversight of the study is guided by the steering committee that is composed of the lead investigators ([name], [name], [name], LT, and [name]). The sponsors of the study are McMaster University and Western University. The sponsors are indemnified for any harms arising from trial participation and they approve protocol amendments when ethics approval has been obtained. Day-to-day running of the study is provided by the trial principal investigators, the study coordinators, and research assistants. The monitoring board consists of three well-established investigators from universities within Canada but outside McMaster and Western Universities.

All case report forms are anonymized using study identifiers and are stored in locked cabinets in a locked office. An administrative assistant to the study team who is not involved in the study holds the key to participants’ names. Research staff who are not involved in data collection enter data in a two-step process (entry and verification, following standard operating procedures) in our REDCap projects hosted at McMaster University [52]. REDCap is a secure, web-based application designed to support data capture for research studies, providing: (1) an intuitive interface for validated data entry; (2) audit trails for tracking data manipulation and export procedures; (3) automated export procedures for seamless data downloads to common statistical packages; and (4) procedures for importing data from external sources. Use of range check for data values promotes data quality. Double data entry is performed to ensure inter-study site reliability.

The research assistant monitors intervention adherence biweekly. For the nutrition portion, this includes ensuring dietary intake meets each participant’s caloric needs and are within an acceptable macronutrient distribution range. In terms of the exercise portion, participants monitor and report biweekly their physical activity using a diary and by wearing a pedometer. Participants report any discomfort experienced (due to the natural course of pregnancy and/or the intervention) to the study coordinator who personalizes the intervention as needed.

### Statistical methods

The analysis and reporting of the results will follow the SPIRIT statement for reporting RCTs [53]. The process of patient selection and flow throughout the study will be summarized using a flow-diagram (Fig. 2).

The results of patient baseline characteristics and outcome variables (both primary and secondary) will be summarized using descriptive summary measures: expressed as mean (standard deviation) or median (range) for continuous variables and n (%) for categorical variables. All statistical tests will be performed using two-sided tests at the 0.05 level of significance. Binary outcomes will be analyzed using logistic regression and continuous outcomes will be analyzed using linear regression. All analyses will account for stratification by including study site and participants’ BMI category in the models. For all models, the results will be expressed as estimate of the difference for continuous outcomes (odds ratio [OR] or relative risk [RR] for binary outcomes), corresponding two-sided 95% confidence intervals (CI) and associated *p* values. *P* values will be reported to three decimal places with values < 0.001 reported as < 0.001. The Hosmer–Lemshow will be used to assess goodness-of-fit for logistic regression and explore the residuals to assess goodness-of-fit and model assumptions for linear regression.

An intention-to-treat principle will be adopted to analyze all outcomes. Multiple-imputation will also be used to handle missing data during data collection. Sensitivity analyses will be performed using some of the commonly used RCT patient-level methods (e.g. generalized estimating equations, the random-effect model which account for the potential correlation within sites, etc.) to assess the robustness of the results [54]. All the analyses will be done using SAS 9.2 (Cary, NC, USA) or SPSS 13 (Chicago, IL, USA). Table 2 provides a summary of the planned methods of analyses for each outcome and subgroup.

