3. Subgroup analyses	The percentage of women within each of the normal, overweight, and obese BMI categories will be similar with respect to being with the IOM target GWG for each category	Proportion of women in each BMI category who reach appropriate GWG according to the IOM guideline for GWGs	Regression analysis including the interaction term of BMI group X Intervention group
4. Sensitivity analyses	Combined Nutrition + Exercise Intervention leads to a greater percentage of women who achieve GWG within current recommendations when compared to standard care	Primary outcome only	***•*** Generalized estimating equations ***•*** Random-effects model

IMPORTANT REMARKS:

In all analyses, results will be expressed as difference or OR (95% CI) and associated *p* values, as appropriate

Bonferroni method will be used to adjust the overall level of significance for multiple secondary outcomes

We will examine residuals to assess model assumptions

The GEE [76] is a technique that allows to specify the correlation structure between patients within a site and this approach produces unbiased estimates under the assumption that missing observations will be missing at random. An amended approach of weighted GEE will be employed if missingness is found not to be at random [77]

*Infant growth outcomes at 6 months will be adjusted for feeding type (duration of breast feeding from birth to 6 months)

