### Power calculation

The sample size calculation for the core study is based on the test of the null hypothesis that the percentages of women with GWG within IOM guidelines in the two populations (intervention and control) are equal. To account for the uncertainty in these prior estimates, we calculated the sample size for different values of the percentage of women with weight within IOM guidelines in the control group in the range of 50–65%, with a risk difference of 15%, 20%, 25%, and 30%. While initially we targeted a total sample size of 350, the constraints of our funding timelines (which include a one-year CHIR grant extension) and a recruitment rate that was less than projected despite our best efforts, we revised our desired sample size to 242. Based on our a priori calculation, a sample size 111 per group corresponds to an absolute difference of 30% with our Nutrition + Exercise intervention, resulting in 30% of women in the treatment group having a GWG exceeding the IOM recommendations compared to 65% in the control group. With the revised sample size (i.e. assuming a 1:1 allocation ratio), the study will have power of 80% to yield a statistically significant result assuming a binomial distribution (using an intention-to-treat principle for the analysis) of the difference between percentages of women with GWG within IOM guidelines at alpha = 0.05. We hope to increase the sample size to 242 total participants in order to allow us to account for the two stratification variables – site (2 degrees of freedom) and baseline BMI strata (3 degrees of freedom).

The calculated sample size for the secondary outcome of maternal bone biomarker status is a total of 177 participants (allocation 1:1, α = 0.05, β = 20 for two-group t-test), based on literature with similar outcomes [55, 56]. A sample size was also calculated for the secondary outcome of infant whole body minus the head BMD. The total is 240 participants (allocation 1:1, α = 0.05, β = 20 for two-group t-test) based on the literature with similar primary outcomes in infant populations [57, 58]. For both sample sizes, a 15% attrition rate was calculated as a precaution in this type of clinical trial with follow-up.

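### The decision level for the secondary outcomes is not settled: a 0.05 rule for every test stands beside a Bonferroni remark with no stated precedence, and the Bonferroni family is defined inconsistently

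*Protocol article*

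**What the plan says.** Statistical methods sets one level for everything: "All statistical tests will be performed using two-sided tests at the 0.05 level of significance". For all models it asks for estimates with "corresponding two-sided 95% confidence intervals (CI) and associated" p values. The section closes by referring the reader on: "Table 2 provides a summary of the planned methods of analyses for each outcome and subgroup".

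The remarks under Table 2 (Outcome measurements) add: "Bonferroni method will be used to adjust the overall level of significance for multiple secondary outcomes". The remark just before it reads "In all analyses, results will be expressed as difference or OR (95% CI) and associated" p values. Neither place gives a divisor or names the outcomes that form the family.

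The Power calculation sizes two secondary bone outcomes. For maternal bone biomarkers the total is "177 participants (allocation 1:1, α = 0.05, β = 20 for two-group t-test". For the infant bone outcome, "The total is 240 participants (allocation 1:1, α = 0.05, β = 20 for two-group t-test". Neither alpha is adjusted.

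The article describes the set of secondary outcomes in two ways:

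- **Bone only.** The list that opens Outcome measurements, and the Specific objectives, count only bone outcomes as secondary. The list puts body weight and fat mass, metabolic status, blood pressure, pregnancy and infant birth outcomes under a separate class of other outcomes.
- **Wider.** The secondary row of Table 2 includes maternal fat mass, glucose, lipids, leptin, adiponectin, blood pressure, gestational diabetes, pre-eclampsia, birth weight z-score and infant fat mass. The abstract also takes a wide view.

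**The concern.** Two statements govern the same secondary outcomes, and the article does not say which one decides. An analyst who follows Statistical methods can call a secondary result significant at p < 0.05 and cite the protocol. One who follows Table 2 needs a much smaller p value, but cannot compute the threshold because the family is not fixed.

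The stake is the bone-health claim. Bone health of mother and offspring is part of the stated hypothesis, and the abstract says that an effective trial will show the importance of early nutrition for offspring bone. If results are judged at 0.05 each, the error control promised in Table 2 is lost. If the family can be chosen after the results are seen, the threshold can be moved to suit them.

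**Working it through.** **Inputs.** Per-test level 0.05, two-sided (Statistical methods). Bonferroni for secondary outcomes with divisor m not stated (Table 2 remarks). Secondary sample sizes 177 and 240 at alpha 0.05, with β = 20 read as 20%, and 15% attrition (Power calculation). Outcome counts are from Outcome measurements.

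**Step 1: the plan's own figures.** The totals 177 and 240 cannot be rebuilt, because no effect size or SD is given. They are consistent with 15% attrition: 150/0.85 = 176.5, rounded up to 177, and 204/0.85 = 240. The implied standardized differences are (1.960 + 0.842) × √(4/150) = 0.46 and (1.960 + 0.842) × √(4/204) = 0.39. What matters here is the alpha used: 0.05 per two-group t-test, which treats 0.05 as the per-test level for secondary outcomes.

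**Step 2: size of the family.** One comparison per marker and specimen is assumed, and the lipid profile is counted as one outcome.

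- Outcome list: 5 markers + 3 maternal DXA + 1 infant DXA = 9. With maternal and cord markers counted separately: 5 + 5 + 3 + 1 = 14.
- Table 2 secondary row: markers 5 (or 10) + maternal DXA 3 + maternal fat mass 1 + glucose, lipids, leptin and adiponectin 4 + blood pressure 2 + pregnancy outcomes 2 + infant DXA 1 + infant outcomes 2 = 20 (or 25).

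**Step 3: threshold and error rate.** The Bonferroni level is 0.05/m. If every test runs at 0.05 with no true effects and independent tests, the chance of at least one false positive is 1 − 0.95^m.

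| m | Bonferroni level | Chance of ≥ 1 false positive at 0.05 per test |
|---|---|---|
| 9 | 0.0056 | 37% |
| 14 | 0.0036 | 51% |
| 20 | 0.0025 | 64% |
| 25 | 0.0020 | 72% |

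Bonferroni holds this chance to at most 5% for any m and any dependence.

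**Step 4: conflicting verdicts.** A secondary result with p = 0.02 is significant under Statistical methods. It fails Bonferroni for any family of 3 or more (0.05/3 = 0.0167). Within Bonferroni the undefined family also matters: p = 0.004 passes at m = 9 and fails at m = 14, and p = 0.003 passes at m = 14 and fails at m = 20 or 25.

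**Step 5: correlation.** Bone outcomes are likely to be correlated, but the article gives no correlations, so these are assumed. Simulating 400,000 sets of 14 equicorrelated normal test statistics gave the following chances of at least one false positive:

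| Assumed correlation | 0.05 per test | Bonferroni (critical value 2.914) |
|---|---|---|
| 0 | 51.2% | 4.9% |
| 0.3 | 43.8% | 4.5% |
| 0.5 | 34.8% | 3.7% |
| 0.7 | 24.9% | 2.7% |

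Correlation lowers both columns, but the gap remains large.

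**The case against.** The best defence is that this is a general rule with a specific modifier. Statistical methods sets a default of 0.05 and then points to Table 2. A Bonferroni adjustment needs a level to adjust, and 0.05 is the only one stated. Read together, 0.05 is the overall level and is divided among the secondary outcomes. That is a common way to write a protocol and is probably what was meant. On that reading the 37% to 72% error rates do not describe the plan, because they arise only if the Bonferroni remark is ignored. The per-test threshold could also be in an analysis plan that is not shown.

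Much of this stands. It does not settle the point, for two reasons. The sentence in Statistical methods covers all tests without exception, and the Power calculation uses 0.05 unadjusted for two secondary outcomes, so the text does not point one way. And an analysis plan can supply a missing divisor, but the article itself already gives two different lists of secondary outcomes.

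A reader might infer that the 95% intervals contradict the Bonferroni test. The documents do not support that. The two remarks sit side by side under Table 2, nominal intervals beside adjusted tests are common, and nothing in the article makes exclusion of the null by a 95% interval the criterion for a claim. A reader might also take 14 as the plan's family. It is only one possible count.

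**Conclusion.** The point holds as an unresolved decision rule. The article does not say that the Bonferroni remark limits the 0.05 default, and it gives two different families to which the remark could apply. Depending on the family, the threshold is about 0.0056, 0.0036 or 0.0020, and secondary p values between that and 0.05 get opposite verdicts. Applying 0.05 per test would raise the family-wise error from at most 5% to about 37%, 51% or 72% under independence (m = 9, 14 or 25), and to about 35% for m = 14 at an assumed correlation of 0.5.

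These sizes rest on counts of m and on correlations that the article does not state. A reader might go further and conclude that the plan has no multiplicity control. It does: Table 2 promises Bonferroni, and the loss occurs only if the 0.05 sentence is followed literally. The primary outcome, tested at two-sided 0.05 with a 95% interval, is unaffected. The correction should be made before unblinding, but the flaw does not make the analysis unworkable.

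**What to change.** - In Statistical methods, limit the 0.05 per-test level to the primary outcome, and state that the secondary outcomes form one family tested at an overall two-sided 0.05.
- Name the members of that family and hence m, stating whether maternal and cord markers count separately. Make the outcome list, the secondary row of Table 2 and the abstract agree. Outcomes left out should be called other or exploratory everywhere.
- Use Holm's step-down procedure in place of plain Bonferroni. Plain Bonferroni is valid, but Holm gives the same family-wise control and is never less powerful.
- Keep the 95% intervals, and label those for secondary outcomes as unadjusted for multiplicity and not used to claim an effect.
- In the Power calculation, say that the secondary sample sizes assume unadjusted alpha.

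The cost is wording only, with no new data. The downside is that fewer secondary results can be called significant than at 0.05 per test. For an outcome with 80% power at 0.05, power under plain Bonferroni is Φ(2.802 − z), with z the two-sided critical value: Φ(2.802 − 2.773) = 51% at m = 9, Φ(2.802 − 2.914) = 46% at m = 14 and Φ(2.802 − 3.090) = 39% at m = 25. That is a reason to keep the named family short.
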